### Overall design

Participants will be PLWH who engage in unhealthy drinking and experience moderate or greater chronic pain recruited nationally via online advertisement. Those who are eligible based on an initial set of online prescreening questions will be contacted by study staff for a more comprehensive phone screening. Those who remain eligible based on the more extensive screening will be scheduled for baseline assessment during which they will provide informed consent, confirm HIV diagnosis, and complete baseline questionnaires administered in an interview format. Staff will also orient participants to the EMA procedures whereby they will complete 5 surveys per day for the following 15 days. After EMA data collection, participants will undergo 1:1 randomization into either the intervention group (INTV) or the control (CTL) group. The INTV condition is a 7-session program designed for weekly delivery through videoconferencing by a health coach. Those in the CTL group meet virtually with the health coach for a single session and be provided with information and resources about alcohol and pain. At three-month outcome assessment, staff will administer questionnaires via interview, prior to another 15 days of EMA data collection. The final study assessment occurs six months after randomization and will include a staff-administered interview and a self-collected blood draw to measure phosphatidylethanol (PEth), a biological marker of alcohol use (see [29]). Participants complete self-collected blood draws at home and with guidance through videoconferencing (Fig. 1).

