### Recruitment, consent, and randomization

Recruitment will take place nationally via online advertisement in virtual patient communities, Google, Facebook, Instagram, health websites, and medical applications. BuildClinical (BC), a company that delivers study specific advertisements to various online platforms, regularly monitors metrics (i.e. percentage of potential participants who view and subsequently click an advertisement) to assess effectiveness and optimize the campaign to improve reach as necessary. When potential participants click on a study advertisement, a website populates containing general information about the trial and a link to a BC pre-screening form for those who are interested. BC pre-screening forms ask for contact information (name, e-mail, telephone number) and assess a preliminary subset of study eligibility criteria (e.g., HIV status, drinking habits, pain level).

If potential participants are eligible based on their responses to the preliminary BC pre-screening, research staff will contact the individual via phone call to confirm pre-screening questions and ask additional eligibility questions. At the time of consent, study staff will visually confirm HIV diagnosis via medical record or ART medication. Eligible and interested participants will take part in an informed consent process via videoconference or phone call and those who provide their consent electronically sign a REDCap [34, 35] form.

Randomization occurs after the baseline assessment phase is completed (described below) and is stratified by both gender and frequency of heavy drinking episodes. The project statistician will generate a list of randomization assignments to be used sequentially based on a permuted blocks strategy.

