#### Assessment instruments

##### Sociodemographic characteristics

Sociodemographic information will be collected during screening and baseline interview and includes the following: age, state and zip code, sex assigned at birth, gender identity, height, weight, sexual orientation and whom they have sex with in their life (men only, women only, both men and women, not had sex), marital status, current spouse/partner, ethnicity, race, primary language, education, employment, insurance, difficulty paying bills, and unhoused status.

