##### Alcohol assessment measures

The primary outcomes for alcohol use include number of alcoholic drinks consumed per week and number of heavy episodic drinking days in the past month (assessed via Alcohol Timeline Followback – 30 days [TLFB-30]; [37, 38]). Alcohol-related consequences will also be assessed using the Short Inventory of Problems-Revised (SIP-R; [39]) as a secondary outcome. A series of measures related to the self-regulation of alcohol use will also be administered, including the Readiness to Change Questionnaire (RTCQ; [40] and Goal Systems Assessment Battery (GSAB; [41, 42]), which provides assessment of value, self-efficacy, self-monitoring, and planning related the goal of moderating alcohol use.

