##### Phosphatidylethanol

PEth biomarker tests will be used as a marker of unhealthy alcohol use, and is an additional outcome to supplement self-report outcome measures [56]. Blood samples will be collected by the participants using a Tasso-M-20 device [57] with guidance from research assistants. The device uses a button that sticks to the skin, typically on the shoulder. When the instrument is pressed, a lancet pierces the skin and draws blood from the capillaries into a container at the bottom of the device. This procedure produces little discomfort and can be used with minimal training.

The full set of assessments is presented in Table 1.

**Table 1 Tab1:** Enrollment, intervention, and assessment schedule

TIMEPOINT	Enrolment	Baseline	Randomization	Month 3	Month 6

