#### Primary and secondary analyses

Descriptive statistics will be provided for the baseline characteristics of the full sample and by condition (i.e., INTV vs. CTL). Multiple linear regression analyses will be used to test whether those in the INTV group consume fewer drinks per week, engage in fewer episodes of heavy episodic drinking, and report lower PEG ratings than those in the CTL group at 6-month outcome. Covariates will include age, sex at birth, and corresponding baseline measures of alcohol use and pain. Secondary analyses will examine related outcomes (i.e. alcohol related consequences, pain intensity, pain severity) using a parallel approach. Exploratory analyses will examine INTV effects on outcomes including substance use frequency, depressive symptoms, anxiety symptoms, HIV symptom index scores, HIV risk-taking behaviors, mental functioning, and physical functioning at 6 months using multivariate regression models. For PEth analyses, we will use the lower limit of quantification as a cut-off of > 50 as a measure of unhealthy alcohol use and a cutoff of PEth > 8 ng/ml) as a marker of any alcohol use. Logistic multiple regression with the age and race/ethnicity will be used to examine intervention effects on 6-month PEth outcomes [101]. Secondary aims will be addressed, in part, by using baseline interview measures of readiness-to-change (for alcohol) and baseline GSAB questionnaire ratings of self-efficacy and planning (for both alcohol and pain outcomes). Planned covariates include those described under primary aims and will include baseline values of the questionnaire measure being evaluated. The Condition x Moderator term will be added to the full models to examine interaction effects, which will be followed with simple slopes analyses to determine the direction of effects.

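### The PEth logistic model omits both randomisation stratifiers and any baseline drinking measure; a smaller mismatch of the same kind affects the primary models

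*Protocol article*

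**What the plan says.** **Randomisation.** Under Overall design, "participants will undergo 1:1 randomization into either the intervention group (INTV) or the control (CTL) group". Under Recruitment, consent, and randomization, allocation "is stratified by both gender and frequency of heavy drinking episodes", and the project statistician will "generate a list of randomization assignments to be used sequentially based on a permuted blocks strategy". Block size and the cut-points for heavy-drinking frequency are not given.

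**Primary and secondary models.** Under Primary and secondary analyses, three linear regressions are planned at 6 months: drinks per week, heavy drinking episodes and PEG. "Covariates will include age, sex at birth, and corresponding baseline measures of alcohol use and pain". Secondary outcomes follow a parallel approach.

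**PEth.** The same section defines two binary outcomes, above 50 and above 8 ng/ml, and states: "Logistic multiple regression with the age and race/ethnicity will be used to examine intervention effects on 6-month PEth outcomes". The Phosphatidylethanol section says that PEth "is an additional outcome to supplement self-report outcome measures". Table 1 schedules it at month 6 only.

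**What is available at baseline.** Table 1 schedules the TLFB at baseline, month 3 and month 6. It supplies the "number of heavy episodic drinking days in the past month (assessed via Alcohol Timeline Followback", as well as drinks per week. Sociodemographic characteristics lists "sex assigned at birth, gender identity, height, weight", so sex at birth and gender are recorded as separate items. Sex at birth is known for everyone, because unwillingness to give it is an exclusion criterion.

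**The concern.** Stratified permuted blocks balance the arms on the stratifiers. If these predict the outcome, the treatment estimate varies less between hypothetical repeats of the trial than under simple randomisation. A model without them does not see this and reports a standard error that is too large. The confidence interval is then too wide and the test rejects too rarely. Leaving out baseline drinking also gives up ordinary covariate precision. The Sample size determination section itself counts a baseline covariate as a source of power.

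This matters most for PEth. Participants know whether they were offered seven sessions or one, so a biomarker is a useful check on self-reported drinking. PEth has no baseline value of its own, so baseline TLFB drinking is the natural substitute. The Discussion also concedes that the feasibility of self-collected, mailed samples is largely unknown, so PEth may be available for fewer people than the interviews are.

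**Working it through.** **1. The plan's own figure.** Inputs from Sample size determination: 250 randomised, 20% attrition, d = 0.40, two-sided alpha 0.05, power 80%.

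- Per arm: n = 2(1.960 + 0.842)² / 0.40² = 98.1, so 99. Total 198 / 0.80 = 247.5, so 248, against 250 stated.
- With 100 per arm: Φ(0.40·√(100/2) − 1.960) = Φ(0.868) = 0.807; the t-test gives 0.804.

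The 80% reproduces from an unadjusted comparison, so it does not depend on the stratifiers.

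**2. Which model holds which stratifier, on the article's wording.**

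| Model | Gender | Heavy-drinking frequency |
|---|---|---|
| Heavy episodes | sex at birth as stand-in | own baseline count |
| Drinks per week | sex at birth as stand-in | related: baseline drinks per week |
| PEG | sex at birth as stand-in | none, if only baseline PEG corresponds |
| PEth | none | none |

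**3. Cost for PEth, by simulation.** From the article: 250 randomised 1:1, 20% lost, stratified permuted blocks. Assumed, because the article gives no values: blocks of 4, 30% women, a two-level heavy-drinking stratum derived from baseline drinking with noise, loss at random, and a positive rate of 1/(1 + e^−0.3) = 57% in controls at average covariates. The log-odds effect is 0.5 for sex. For the stratum and for baseline drinking (per SD) it is 1.0 and 0 (weak), 0.7 and 0.7 (moderate), or 1.0 and 1.2 (strong). There were 1,500 trials per setting.

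No treatment effect:

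| Prognosis | Model SE, as written | True SD, as written | SE/SD | Rejection, as written | Rejection, strata added |
|---|---|---|---|---|---|
| Weak | 0.290 | 0.275 | 1.05 | 3.3% | 4.3% |
| Moderate | 0.290 | 0.277 | 1.05 | 4.1% | 5.2% |
| Strong | 0.289 | 0.259 | 1.12 | 2.7% | 5.1% |

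Simulation error of a 5% rejection rate is √(0.05·0.95/1500) = 0.6 points, so 5.2% and 5.1% are compatible with 5%.

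Power, treatment log-odds −0.9:

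| Prognosis | Age + race/ethnicity | + sex and heavy-drinking stratum | + baseline drinking | Total gain |
|---|---|---|---|---|
| Weak | 84.3% | 86.7% | 86.7% | 2.4 |
| Moderate | 72.1% | 78.2% | 79.2% | 7.1 |
| Strong | 53.3% | 66.3% | 69.6% | 16.3 |

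The strata alone give 2.4, 6.1 and 13.0 points; baseline drinking adds 0, 1.0 and 3.3. (Rounding to whole percentages before subtracting, 70 − 53, turns the largest loss into 17.)

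**4. Cost for PEG, by simulation.** The linear model already holds sex and baseline PEG (assumed correlation 0.5 with the outcome), d = 0.40, 3,000 trials per setting. Adding the heavy-drinking stratum:

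| Stratum–outcome correlation | Power without | Power with | Gain | Null rejection without |
|---|---|---|---|---|
| 0.1 | 90.0% | 90.2% | 0.2 | 4.8% |
| 0.2 | 90.8% | 91.8% | 0.9 | 4.6% |
| 0.3 | 90.5% | 92.6% | 2.1 | 3.7% |

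Gains are taken before rounding.

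**The case against.** **The primary models are largely sound.** A reader might infer that all the models ignore both stratifiers. The article does not support that: the first three rows of the table in step 2 show sex at birth in every primary model and a baseline drinking measure in both alcohol models. PEG lacks a drinking term only if the covariate sentence pairs each outcome with its own baseline. The Primary aim, which controls for corresponding baseline values, favours that reading, but the sentence could also mean that alcohol and pain baselines enter every model. This objection stands, and the point is confined accordingly.

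**Gender may simply mean sex at birth.** The eligibility thresholds are set for women and men, and sex at birth is mandatory, so the stratifier may be sex at birth under a loose label. That is possible. Because the two are recorded separately, the wording needs reconciling, but it does not prove that the models drop the stratifier.

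**The PEth loss rests on assumptions.** This also stands. PEth is a supplementary outcome with no power claim, only one positive rate was simulated although two cut-offs are planned, and the prognostic strengths are guesses. The direction is firm; the size is a range.

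**The full plan may add strata.** For the primary models this is plausible, since their list says only what covariates will include. It does not rescue PEth, where the article names a specific and different set. The source cited for that choice could not be consulted.

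**Two further inferences fail.** The PEth odds ratio is not biased by the omission. Odds ratios are non-collapsible, so the shorter model estimates a more marginal odds ratio, closer to 1, which is a different quantity. Nor can PEth be called the only outcome without baseline adjustment, because no covariates are stated for the exploratory outcomes.

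**Conclusion.** The point holds for PEth. The model as written has neither stratifier and no baseline drinking measure, although the data for both are collected at baseline. Its standard errors run about 5 to 12% above the true sampling variation in the settings tried, and roughly 2 to 16 points of power are lost, depending on how strongly the stratifiers and baseline drinking predict PEth. For the primary models it is a matter of consistency: gender against sex at birth, and a missing heavy-drinking term for PEG that is worth about 0 to 2 points.

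It would be wrong to conclude that the trial risks false positives or that its stated power fails. No setting inflated type I error, and the 80% figure stands. The primary conclusions are little affected. The change is worth making because it is nearly free and strengthens the one alcohol measure that does not rely on self-report.

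**What to change.** Before outcome data are examined by arm:

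- **PEth:** keep age and race/ethnicity. Add both stratification factors, with the categories used at randomisation, and baseline TLFB drinking, for example drinks per week.
- **Primary and secondary models:** add the stratification factors wherever they are absent, in particular heavy-drinking frequency for PEG and the pain outcomes.
- **Gender or sex at birth:** state which variable defined the strata and use the same one for adjustment.
- **Reporting:** say that the PEth odds ratio is conditional on the listed covariates, since adding them changes what it estimates.

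Possible wording: *Each 6-month PEth outcome will be analysed by logistic regression on condition, age, race/ethnicity, the two stratification factors as coded at allocation, and baseline drinks per week. All primary and secondary models will also include the stratification factors.*

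The cost is a sentence or two of analysis text and a few degrees of freedom. No new data and no change to the sample size are needed.

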### Rationale for study design

The study is designed to test the efficacy of INTV, but has several additional objectives including, (1) the use of a nationally representative sample, (2) implementation of all study procedures remotely, (3) being able to identify potentially important moderators of intervention efficacy, and (4) providing detailed analyses of the processes through which the intervention may impact outcomes. Recruitment through social media will target PLWH across the country in areas defined by the CDC as having high HIV prevalence rates. This fully remote approach reduces participant burden and increases study efficiency. Finally, the study design incorporates the use of EMA. Multilevel modeling allows for an examination of how treatment may change associations between contextual cues (e.g., mood) and outcomes of interest (e.g., drinking, pain) over time. This approach enables fine-grained analysis of how the intervention may impact pain, alcohol use, and their interaction, in addition to providing insight into psychological processes (e.g., self-efficacy) through which these influences may occur. Such information will provide insight into how and for whom the interventions may reduce heavy drinking and pain.

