### Statistical design and analysis

#### Sample size determination

A sample size of 250 (*n* = 125 to each condition) will be randomized. With a conservative estimate of a 20% attrition rate by 6-month follow-up, this sample size gives power (80%) to detect medium effects (Cohen’s d = 0.40) at the 2-tailed significance level (0.05) for INTV versus CTL at 6-month follow-up on both pain and alcohol outcomes. The anticipated effect size is based on the following: (1) meta-analyses of CBT interventions compared to assessment and minimal interventions suggesting medium post-intervention effects on alcohol and pain; [98–100] and (2) results of our pilot study which showed medium-to-large pre-to-post changes (Cohen’s d from 0.79 to 1.0) within participants receiving INTV [95, 96]. Moreover, the availability of repeated measurements (to include a baseline covariate) increases statistical power to detect intervention effects for the analysis.

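### In the alcohol moderator models, Condition x Moderator is the only interaction named, so a moderator that tracks baseline drinking can be credited with an effect difference that belongs to drinking level.

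*Protocol article*

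**What the plan says.** Under Primary and secondary analyses, the protocol article fits multiple linear regressions to drinks per week, heavy-drinking episodes and PEG at 6 months. The covariates are age, sex at birth and the baseline value of the outcome.

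The moderator analyses keep these covariates and add the baseline score of the questionnaire under test. The step that tests moderation is this: "The Condition x Moderator term will be added to the full models to examine interaction effects". Simple slopes come afterwards, to show which way an interaction runs. No product of Condition with any other baseline variable is named.

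Under Secondary aims, the alcohol moderators are baseline readiness-to-change and the GSAB ratings of self-efficacy and planning, and the hypothesis is that they moderate the INTV effect.

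**The concern.** Randomisation protects the comparison of INTV with CTL. It does not settle which of several correlated baseline traits a varying treatment effect belongs to.

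The models are linear in numbers of drinks. Under an assumed 30% reduction, a participant at 14 drinks a week loses 0.30 x 14 = 4.2 drinks and one at 28 loses 0.30 x 28 = 8.4. A constant percentage effect is therefore a Condition x baseline-drinking interaction on the analysis scale. A main effect of baseline drinking cannot absorb it. Stratifying the randomisation by heavy-drinking frequency balances the arms, but leaves any correlation between moderator and baseline drinking in place.

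The eligibility criteria make a wide spread of baseline drinking likely: they run from a single heavy occasion in the past month to unlimited weekly intake. The moderators concern the drinking itself, so some correlation with its level is plausible. If both conditions hold, a significant readiness interaction could be reported as evidence about self-regulation when it shows only that heavier drinkers had more drinks to lose.

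**Working it through.** **Inputs from the protocol article.** "A sample size of 250", with 125 per arm; "a conservative estimate of a 20% attrition rate by 6-month follow-up"; "participants will undergo 1:1 randomization"; two-sided 5% level; d = 0.40. Completers: 250 x 0.80 = 200, or 100 per arm.

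**The plan's own figure.** The standard error of the standardised difference is sqrt(2/100) = 0.1414, so z = 0.40/0.1414 = 2.83 and power = Phi(2.83 - 1.96) = 0.807 (0.804 with the noncentral t). The article's "this sample size gives power (80%) to detect medium effects" reproduces. That figure is for the main effect, which this point does not touch.

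**Assumed, not in the documents.** The correlation r between moderator and baseline drinking; how the INTV effect varies with baseline drinking; the distribution of drinks; and the baseline-to-follow-up stability. In every case below, the moderator has no role of its own.

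**Hand check, standardised normal outcome.** Let the effect grow by g SD per SD of baseline, with baseline-outcome correlation 0.5 (residual variance 0.75).
- With Condition x baseline omitted, the Condition x Moderator coefficient tends to g x r in size.
- Its standard error is about 2 x sqrt(0.75 + g^2(1 - r^2)/4)/sqrt(200).
- Rejection is about Phi(z - 1.96) + Phi(-z - 1.96).

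| g | r | coefficient | SE | z | formula | simulated |
|---|---|---|---|---|---|---|
| 0.2 | 0.1 | 0.02 | 0.123 | 0.16 | 5.3% | not run |
| 0.2 | 0.3 | 0.06 | 0.123 | 0.49 | 7.8% | 7.5% |
| 0.2 | 0.5 | 0.10 | 0.123 | 0.81 | 12.8% | 12.6% |
| 0.4 | 0.3 | 0.12 | 0.125 | 0.96 | 16.0% | 15.4% |
| 0.4 | 0.5 | 0.20 | 0.125 | 1.60 | 36.0% | 34.9% |

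Simulations here and below use 200 completers and 2,000 trials per setting, except where the number is not stated. With Condition x baseline added, the simulated rates at r of 0.3 and 0.5 are 4.7 to 6.0%.

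**Log-normal drinks, constant percentage reduction.** Rejection of Condition x Moderator at nominal 5%:

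| Setting | r = 0.3 | r = 0.5 |
|---|---|---|
| A: 30% reduction | 7.0% | 13.2% |
| A: 40% reduction | 9.8% | 16.3% |
| A: 35% reduction, stability 0.75 | 13.0% | 26.0% |
| B: 25% reduction | 8.4% | 13.3% |
| B: 25% reduction, HC3 | 6.8% | 9.3% |
| B: 40% reduction | 11.4% | 23.5% |
| B: 40% reduction, HC3 | 9.2% | 17.8% |

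Set B takes a median of 15 drinks a week, a log SD of 0.7, follow-up proportional to baseline to the power 0.6, and a log-scale residual SD of 0.5. A further set of runs at r of 0.3 to 0.5 gave about 9 to 32%, and about 6 to 24% with HC3. Adding Condition x baseline outcome brought the rates to 4.8 to 8.0% in set A, 4.9 to 6.0% in set B at these correlations, and about 5 to 7% in the further set.

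**Null cases.** In the normal model with a constant absolute effect (g = 0), the planned test stays at 4.2 to 5.6%. With r = 0 it stays at 4.4 to 5.6% in all models.

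**Cost of the extra term.** Variance inflation is about 1/(1 - r^2). At r = 0.3 it is 1/0.91 = 1.10, so the standard error rises by a factor of 1.05. At r = 0.5 it is 1/0.75 = 1.33, a factor of 1.15.

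**The case against.** The strongest reply is that these rejections are not false positives in the plain sense. Under the assumed truth, the INTV effect in drinks really is larger at moderator levels that go with heavier drinking. The planned test detects that, and the article does not say that its moderators act independently of drinking level. This stands. The error arises only when the result is credited to readiness, self-efficacy or planning as such. Even the adjusted term would not make the attribution causal, because baseline traits are not randomised.

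Second, the size depends on assumptions. At the mildest setting (30% reduction, r = 0.3) the planned rate of 7.0% lies within the 4.8 to 8.0% seen after the extra term. This stands, so the size must be given as a range with its null cases.

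Third, part of the excess is unequal variance from linear models on skewed counts. In one check with log SD 0.8 and stability 0.6, HC3 errors alone took the planned test from 12.9% to 8.0% (30%, r = 0.5) and from 17.7% to 12.4% (40%, r = 0.5). That explains part of it, but not all.

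Fourth, an unseen analysis plan could add the term. It could, but the article does state the model, and states it without the term.

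A reader might also infer that one significant and one non-significant simple slope would be taken as moderation. The text does not support this: "which will be followed with simple slopes analyses to determine the direction of effects" is the usual sequence after an interaction test, and an unwritten gate is detail that an article may leave out. Nor does "Such information will provide insight into how and for whom the interventions may reduce heavy drinking and pain" show that the interview moderator models claim independent moderation, because that sentence follows a description of EMA and multilevel modelling.

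**Conclusion.** The point holds as one of attribution. As specified, a significant Condition x Moderator term for drinks per week or heavy-drinking episodes cannot distinguish moderation by self-regulation from a larger absolute effect in heavier drinkers. At correlations of 0.3 to 0.5 and proportional reductions of 30 to 40%, the term rejects in about 7 to 32% of simulated trials (about 6 to 24% with HC3) with no role for the moderator itself. With a correlation near 0.1, or a constant number of drinks removed, there is little or no inflation. The documents give neither the correlation nor the form of the effect.

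A reader might infer that the moderator test is invalid, or that the same holds for every moderator model. The documents do not support either reading. The test is sound as prediction. The article does not set out the product terms of the EMA moderator model, and the proportional-effect argument was worked through for drinking counts, not for PEG, which is a bounded rating. The primary comparison and the sample size are untouched.

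**What to change.** For the alcohol-outcome moderator models under Primary and secondary analyses:

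- Keep the planned model, and also fit and report one that adds Condition x baseline value of the same outcome.
- Give the Condition x Moderator estimate with its 95% interval from both models.
- Claim moderation by readiness, self-efficacy or planning in its own right only if it holds with the added term. Otherwise describe the finding as a predictive difference that drinking level may explain.

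This takes one product term per model, with no new data and no change in sample size. The price is precision in the added model, where the standard error of the moderator interaction rises by about 5% at a correlation of 0.3 and up to 15% at 0.5, in a trial sized for main effects. Reporting both models keeps the planned estimate available.
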